#### Primary Aim

The primary aim is to examine differences in psychological (craving, sense of presence, and social presence) and physiological (eye gaze, HR, and EDA) responses between young adults who currently vape and those who have never vaped during exposure to VR vaping cues presented with and without social pressure. We hypothesize that vapers will exhibit stronger craving, a greater sense of presence and social presence, increased visual attention to vaping cues, and heightened physiological arousal compared with nonvapers across both VR scenes. We further expect that both groups will show stronger psychological and physiological responses in the social pressure condition than in the no pressure condition.

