## Methods

### Study Design

This study will examine individuals’ psychological, behavioral, and physiological responses to e-cigarette cues in VR among young adults aged 18 to 21 years. We focus on this age range because the transition into early adulthood often brings increased exposure to vaping-related social contexts (eg, college gatherings) [27], and this pilot allows us to first test the paradigm in adults before adapting it for adolescent populations. A between-subjects design is used to compare current e-cigarette users and nonusers, with a within-subject, counterbalanced component to assess 2 cue conditions (with and without social pressure). This mixed-design approach enables testing of cue effects and group differences while controlling for individual variability.

Prior VR nicotine cue reactivity studies have reported medium-to-large effects for the response difference between user and nonuser groups [17,28]. Based on the relevant research and using G*Power 3.1 (Heinrich Heine University Düsseldorf) for a 2 (group: vapers vs nonvapers)×2 (cue condition: social pressure vs no social pressure) mixed design, we powered the study for the group × cue condition interaction (group×cue condition) assuming a medium effect (*f*=0.25; partial η-squared ≈ 0.06; power=0.80). We assumed a within-participant correlation of *r*=0.50 between cue conditions and a nonsphericity correction of *ε*=1.0 (sphericity is not applicable with 2 within-subject levels). This yields a minimum required sample of 34 (n=17 per group). To ensure robustness and account for potential data loss (eg, eye-tracking dropout and physiological artifacts), we plan to recruit 40 participants in total (n=20 vapers and n=20 nonvapers).

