##### Primary Analyses

For the primary aim of examining differences in psychological and physiological responses between vapers and nonvapers during VR cue exposure with and without social pressure, a mixed-model ANOVA will be conducted. Group (vapers vs nonvapers) will serve as the between-subjects factor, and cue condition (social pressure vs no social pressure) as the within-subjects factor. If the assumptions of normality or homogeneity of variance are violated, nonparametric alternatives such as the aligned rank transform ANOVA [55] will be used to preserve the ability to test interaction effects within the mixed design. Follow-up pairwise comparisons will be conducted with Bonferroni-adjusted *P* values.

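### Holm in place of Bonferroni for the follow-up comparisons would keep the same familywise error control and, in the scenarios checked, add roughly 1 to 11 points of power per real contrast

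*Protocol article*

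**What the plan says.** Under Primary Analyses the article plans that "a mixed-model ANOVA will be conducted", with group between subjects and cue condition within subjects, and an aligned rank transform version if assumptions fail. The section then adds: "Follow-up pairwise comparisons will be conducted with Bonferroni-adjusted" P values. It names no step-down procedure, so the plain reading is single-step Bonferroni. It does not list the comparisons in the family.

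The Primary Aim makes two directional predictions. Vapers are to respond more strongly "compared with nonvapers across both VR scenes", and "both groups will show stronger psychological and physiological responses in the social pressure condition" than without pressure.

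Study Design says "we powered the study for the group × cue condition interaction" at f = 0.25 ("partial η-squared ≈ 0.06; power=0.80"), with a correlation of 0.50 between conditions. The required total is 34 and the planned total is 40, that is 20 per group. The follow-up comparisons are not separately powered.

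**The concern.** If the Primary Aim is read scene by scene and group by group, its predictions are four simple effects: vapers against nonvapers in each of the two scenes, and pressure against no pressure in each of the two groups. If the interaction that the study is powered for is present, the averaged main effects do not show whether a prediction holds in each scene or group, so these four contrasts would carry the interpretation.

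Single-step Bonferroni holds every contrast to the strictest threshold, however many of the others have already been rejected. Holm relaxes the threshold after each rejection and still controls the familywise error under any dependence. When several contrasts are truly non-null, as the Primary Aim expects, Bonferroni gives up power for no gain in error control. What is at stake is how many of the real simple effects a study with 20 per group would detect.

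**Working it through.** **Inputs.** From Study Design: 20 per group, correlation r = 0.50, f = 0.25, power 0.80. Assumed, because the article does not state them: two-sided alpha 0.05; a family of the four simple effects; normal outcomes with SD 1; effects of 0.5 or 0.8 SD.

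**The plan's own figure.** For the interaction, λ = f²·N·m/(1 − r) = 0.0625 × N × 2 / 0.50 = 0.25N, with 1 and N − 2 df. Power is 0.795 at N = 33, 0.807 at N = 34 and 0.869 at N = 40, so the stated 34 reproduces at alpha 0.05.

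**The powered interaction in SD units.** The SD of a within-person difference is √(2(1 − 0.50)) = 1. For a difference of differences δ with 20 per group, λ = δ²/(2/20) = 10δ². At N = 40, λ = 0.25 × 40 = 10, so δ = 1.0 SD.

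**The two procedures.** Bonferroni compares each of the four P values with 0.05/4 = 0.0125. Holm orders them and compares the smallest with 0.05/4 = 0.0125, the next with 0.05/3 = 0.0167, then 0.05/2 = 0.025, then 0.05, stopping at the first failure. Two facts follow without simulation. Holm rejects everything that Bonferroni rejects. The first step is identical, so the chance of at least one rejection is the same.

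**Bonferroni power per contrast (threshold 0.0125).**
- Group contrast, noncentrality d·√(20/2): 0.16 for d = 0.5 and 0.47 for d = 0.8.
- Scene contrast, noncentrality d·√20: 0.33 for d = 0.5 and 0.78 for d = 0.8.

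The means per contrast are (0.16 + 0.33)/2 ≈ 0.25, (0.47 + 0.33)/2 = 0.40 and (0.47 + 0.78)/2 ≈ 0.63.

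**Bonferroni against Holm by simulation** (independent t tests between groups, paired t tests within groups; group gap and scene effect the same throughout, so no interaction):

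| Group gap / scene effect | Mean power per contrast, Bonferroni | Holm | At least one rejection, both methods |
|---|---|---|---|
| 0.5 / 0.5 SD | 0.25 | 0.28 | 0.65 |
| 0.8 / 0.5 SD | 0.40 | 0.48 | 0.82 |
| 0.8 / 0.8 SD | 0.63 | 0.74 | 0.98 |

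With no true effects, the familywise error is 0.046 under both methods.

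**With the powered interaction** (vapers rise from 0 to 1.0 SD under pressure, nonvapers flat), the two real contrasts are:
- vapers against nonvapers under pressure: 0.70 with Bonferroni, 0.74 with Holm;
- pressure against no pressure in vapers: 0.94 with Bonferroni, 0.95 with Holm.

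**Tests that the choice does not touch.** The 1-df ANOVA tests need no pairwise adjustment. At 20 per group, main-effect power is 0.43 for a 0.5 SD group gap, 0.81 for a 0.8 SD group gap and 0.87 for a 0.5 SD scene effect.

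**The case against.** The case against is substantial, and most of it stands as a limit on size.

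- **Bonferroni is valid.** The article states nothing wrong here and contradicts nothing. That stands: this is an efficiency point.
- **The ANOVA may already answer the aim.** A reader might infer that Bonferroni makes the Primary Aim's predictions needlessly hard to confirm. The documents do not support that. Both predictions can be read as the group and cue main effects, which are tested without adjustment. The main constraint on the follow-ups is sample size: a single 0.5 SD group contrast has power of only about 0.35 with no adjustment at all (normal approximation).
- **A joint claim needs no correction.** A reader might point to the chance of showing all four contrasts, which rises from 0.20 to 0.45 when all effects are 0.8 SD. If the claim is that all four must hold, an intersection-union argument permits unadjusted tests, and the figure is then about 0.48. The rise is therefore not good evidence for Holm.
- **Six pairs is an assumption.** A reader might take pairwise to mean all six cell pairs, including the two that change group and scene together, and so find a larger loss. The article never says those pairs will be tested, and an analysis plan may define the family.
- **The larger gains are favourable cases.** They need most contrasts to be truly non-null at once. With the powered interaction in vapers alone the gain is small.
- **Intervals.** Bonferroni has simple matching simultaneous intervals and Holm does not. In a pilot, where estimates matter, that is a fair reason to hesitate.

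None of this shows Bonferroni doing better on error control or power. The intervals are the only real cost.

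**Conclusion.** The point holds as a small, nearly free improvement. Holm gives the same familywise error control and never rejects less. At 20 per group, the gain in mean power per contrast is about 4 points with 0.5 SD effects throughout and about 8 to 11 points when the group gap is 0.8 SD. It is about 1 to 4 points for the two real contrasts if the powered interaction comes from vapers alone. These figures rest on the assumed four-contrast family, two-sided alpha 0.05, normal outcomes and the protocol's own r = 0.50. The article does not define the family, so the exact loss cannot be fixed from it. The ANOVA tests, the sample size and the validity of the planned analysis are not in question.

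**What to change.** Replace the follow-up sentence in Primary Analyses with: *Follow-up comparisons are the four simple effects (vapers vs nonvapers in each scene; social pressure vs no social pressure in each group), with Holm-adjusted P values within each outcome.* The adjustment works on P values, so it also applies if the aligned rank transform is used.

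Data collection is under way (7 participants as of March 2026), so record the change with its date, for instance as an update to the Open Science Framework registration, before any group comparison is run.

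The cost is one sentence and a software option. Because Holm has no equally simple simultaneous intervals, show unadjusted or Bonferroni intervals beside the Holm P values and label which they are.

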##### Secondary Analyses

For the secondary objective, we will assess associations between multimodal physiological measures and subjective vaping-related outcomes. Correlation and regression analyses will first be conducted to examine pairwise relationships among eye-gaze metrics (eg, total fixations and mean fixation duration), HR, EDA, and subjective measures (eg, craving, dependence scores, and motivation to quit or susceptibility to initiate use). Depending on data distribution, the Pearson or Spearman correlations will be used. Partial correlations or multiple regression models will account for potential covariates such as age, gender, and other substance use.

To further explore multivariate relationships between physiological responses and vaping-related outcomes, exploratory regularized regression analyses will be conducted. Given the pilot sample size, we will use regularized logistic regression with the least absolute shrinkage and selection operator to examine whether aggregated physiological and subjective measures are associated with vaping status (vaper vs nonvaper). Candidate predictors will include summary features derived from eye-gaze behavior (eg, fixation count, proportion of fixation duration on vaping-related cues, and time to first fixation), HRV metrics derived from photoplethysmography signals (including time-domain indices such as root mean square of successive differences and frequency-domain measures such as low-frequency to high-frequency ratio), EDA (eg, mean number of SCRs, mean SCR amplitude, and mean skin conductance level), and relevant subjective responses (eg, craving, presence, and social presence).

Physiological signals will undergo standard preprocessing procedures, including signal quality checks, removal of segments affected by motion artifacts or signal instability, and aggregation into scene-level summary features. Participants will be excluded if more than 15% of their physiological data is missing, and EDA signals will be removed if more than 15% of values are zero or negative, indicating poor sensor contact [56,57]. The regularization parameter will be selected using cross-validation to reduce overfitting [58]. Given the exploratory nature of this analysis and the modest sample size, findings will be interpreted cautiously and used to identify candidate multimodal markers for future confirmatory studies rather than to develop generalizable prediction models.

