#### Secondary Aim

The secondary aim is to assess correlations between multimodal physiological measures (eye tracking, HR, and EDA) and subjective vaping-related outcomes, including craving, sense of presence, social presence, nicotine dependence, and quitting intention (among vapers), as well as susceptibility to initiate vaping (among nonvapers). We hypothesize that psychophysiological responses during VR cue exposure will be significantly associated with subjective vaping-related measures, such that greater attentional and autonomic reactivity will correlate with higher craving, dependence, and quit intention among vapers, and with higher susceptibility to initiate vaping among nonvapers. As an exploratory analysis, we will further examine whether combinations of physiological and subjective measures predict vaping status (vaper vs nonvaper).

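### The secondary aim predicts significant correlations and tests many pairs with no key pair and no error control, while the Abstract calls the same work exploratory

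*Protocol article*

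**What the plan says.** The Secondary Aim (Introduction, Aims) is put as a significance hypothesis: "We hypothesize that psychophysiological responses during VR cue exposure will be significantly associated with subjective vaping-related measures". It then gives a direction: "greater attentional and autonomic reactivity will correlate with higher craving, dependence, and quit intention among vapers", and likewise higher susceptibility to initiate among nonvapers. The aim lists three physiological modalities (eye tracking, HR, EDA) and six subjective outcomes: craving, presence, social presence, dependence, quitting intention and susceptibility. Four of the six carry a stated direction.

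The Secondary Analyses section (Methods, Analysis) carries this out as follows: "Correlation and regression analyses will first be conducted to examine pairwise relationships among eye-gaze metrics (eg, total fixations and mean fixation duration), HR, EDA" and the subjective measures. The metrics are given as examples. The choice between Pearson and Spearman is left to the data, and partial correlations or multiple regressions may follow. Signals are reduced by "aggregation into scene-level summary features", and there are two cue scenes.

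The only multiplicity adjustment in the article is in the Primary Analyses section: "Follow-up pairwise comparisons will be conducted with Bonferroni-adjusted" P values. In the Secondary Aim the exploratory label introduces a different analysis: "As an exploratory analysis, we will further examine whether combinations of physiological and subjective measures predict vaping status (vaper vs nonvaper"). In the Secondary Analyses section the sentence promising cautious interpretation follows the penalised logistic regression (LASSO) and refers to it. By contrast, the Objective in the Abstract and the last paragraph of the Background say that the study will explore these associations.

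**The concern.** The article gives one set of correlations two roles. In the Abstract and Background they are exploration. In the Secondary Aim they are a hypothesis that significance tests will settle. Under the second role the reader needs to know which pair or pairs decide the matter and how error over the family is limited, and neither is fixed. The protections the authors did write (Bonferroni, the exploratory label, the promise of caution) sit on other analyses.

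The group-specific outcomes make this worse. Dependence, quit intention and susceptibility each rest on about 20 people, so a pair that reaches significance by chance will also show a large correlation. The Prospects and Conclusions sections look to the study for markers of addiction and susceptibility and for modelling of intentions. A chance pair could therefore be carried into later work as a candidate marker without the caution that the LASSO results will receive.

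**Working it through.** **Inputs.** 20 vapers and 20 nonvapers (Study Design). Three modalities, or four named metrics if total fixations and mean fixation duration are counted separately (Secondary Aim; Secondary Analyses). Six subjective outcomes, four with a stated direction (Secondary Aim). Alpha is not stated; two-sided 0.05 per test is assumed.

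**Is 0.05 a fair assumption?** The only sample-size figure in the article is 34, for the group by cue condition interaction. With f = 0.25, m = 2 conditions and ρ = 0.50, the noncentrality is λ = f²·N·m/(1−ρ) = 0.0625 × 34 × 2/0.5 = 8.5 on (1, 32) degrees of freedom. At alpha 0.05 the power is 0.807; at N = 33 it is 0.795. The stated 34 reproduces, so 0.05 fits the authors' own calculation. No error rate or power is given for the correlations.

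**Number of tests.** Narrowest: 3 modalities × 4 directional outcomes = 12. All listed outcomes: 3 × 6 = 18. Four named metrics: 4 × 6 = 24.

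**Independent tests, no true association.** A significant result in the hypothesised direction has probability 0.025 per test, so P(at least one) = 1 − 0.975^k:
- k = 12: 26.2%
- k = 18: 36.6%
- k = 24: 45.5%

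Counting either direction, 1 − 0.95^k gives 60.3% for k = 18 and 70.8% for k = 24.

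**Dependent tests.** Measures within a block are correlated, which lowers these figures. In a null simulation the physiological block was independent of the subjective block, with equal correlation within each block. Craving, dependence and quit intention were tested in 20 vapers, susceptibility in 20 nonvapers, and presence and social presence in all 40. Testing craving in all 40 changes little.

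| Tests | Hypothesised direction: within-block correlation 0 / 0.5 / 0.8 | Either direction: 0 / 0.5 / 0.8 |
|---|---|---|
| 12 | 26% / 21% / 14% | not shown |
| 18 | 37% / 26% / 17% | 60% / 50% / 33% |
| 24 | 46% / 32% / 19% | 71% / 58% / 39% |

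The entries at correlation 0 are the closed-form values; simulation agrees to within about two percentage points. The nominal rate for one test in the stated direction is 2.5%, so even the narrowest family runs at 14/2.5 ≈ 6 to 26/2.5 ≈ 10 times that.

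**More tests.** If each scene were tested separately with four metrics, there would be 4 × 6 × 2 = 48 tests. The chance in the hypothesised direction would then be 1 − 0.975^48 = 70% if independent, and about 53% at within-block correlation 0.5.

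**Size of a chance finding.** The critical |r| at two-sided 0.05 is 0.44 for n = 20 and 0.31 for n = 40.

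**The case against.** A reader might infer that a supporting correlation is more likely than not to appear by chance. The article does not bear that out. The hypothesis is directional, so a significant negative correlation counts against it. In the hypothesised direction the chance stays below one half for 12, 18 and 24 tests. With independent tests it passes one half only from 28 tests (1 − 0.975^28 = 50.8%). Testing by scene would exceed that number, but the text does not fix it.

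A reader might also infer that nothing labels these correlations exploratory. That is wrong for the article as a whole: the Abstract and Background use exploratory language, and the study is called a pilot. The document is inconsistent, not silent.

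The rule that any single significant pair would support the hypothesis is an inference too. The Secondary Aim could be read as requiring attentional and autonomic reactivity to track every named outcome, and the at-least-one error rate would not describe that rule. Presence and social presence are in the aim's list but not in its directional clause, which is why the 12-test family is shown.

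Finally, an article condenses a fuller plan, and uncorrected secondary correlations are common in a 40-person pilot. This would dispose of a complaint that details are merely missing. It does not dispose of this one: the article itself states a significance hypothesis, specifies pairwise testing, assigns a correction to one family and caution to another, and describes the same associations elsewhere as exploration. Those statements need reconciling whatever a fuller plan contains.

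**Conclusion.** The point stands in a limited form. The Secondary Aim makes a directional significance claim, the Secondary Analyses section tests it over at least 12 to 24 pairs with no key pair and no error control, and the Abstract and Background give the same work a different status. With no true association, the chance of at least one significant pair in the hypothesised direction is about 14% to 26% (12 tests), 17% to 37% (18) or 19% to 46% (24), against 2.5% for a single test. Counting either direction it is about 33% to 60% (18) or 39% to 71% (24). More metrics or testing by scene would raise all of these.

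The figures assume two-sided 0.05 per test, 20 per group, within-block correlation between 0.8 and 0, and that one significant pair would be taken as support. The change is worth making but is not critical: this is a secondary aim of a pilot, and wording alone corrects it.

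**What to change.** **Preferred.** Bring the Secondary Aim into line with the Abstract and Background. Extend the exploratory label and the cautious-interpretation sentence to the whole correlation analysis. Replace the prediction of significance with estimation of the correlations. Report every pair examined with its 95% CI and a Benjamini-Hochberg q-value. The cost is that no confirmatory secondary claim can be made.

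**If a confirmatory secondary claim is wanted.** Name one summary feature per modality and one subjective outcome per group, control those tests by Holm at 5%, and call all other pairs exploratory. Three features × two group-specific outcomes = 6 tests, so the first Holm step is 0.05/6 = 0.0083, which at n = 20 needs |r| of about 0.57 to 0.58 instead of 0.44.

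Bonferroni over all 18 pairs is less workable. The per-test level is 0.05/18 = 0.0028, the critical |r| at n = 20 rises to 0.63, and power for a true r of 0.5 falls from 62% to 23%.

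Either option changes wording only and needs no new data. The Results section reports data from 7 participants as of March 2026. If enrolment is still near that point, the choice can be made and dated before most data exist.
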